### Effectiveness

To determine effectiveness, investigators will: compare CRC screening rates of passive and active dissemination approaches by setting; examine baseline/post CRC screening rates (community coalition catchment area) and compare baseline/post CRC knowledge attitudes; and beliefs of facilitators (training) and participants (EPICS sessions). Effect size will be computed by subtracting mean CRC screening rates in communities aware and not aware of EPICS divided by the pooled standard deviation of CRC screening rates. The proportion of community coalitions and settings aware of EPICS (effectiveness-organizational level) and that deliver it (adoption) will also be determined.

### Adoption

In evaluating adoption, methods include: determining EPICS fit, cost, level of resources and expertise and similarity to current programs; estimating adoption rate (proportion of community coalitions trained that implement EPICS); and documenting reasons for not adopting EPICS (time, total membership or infrastructure, partnerships, program priorities). Descriptive statistics will be used to provide insight into organizational and individual reasons for (not) adopting EPICS. Differences between community coalitions adopting and not adopting EPICS and differences between facilitator characteristics will be analyzed using independent sample *t* tests and chi-square tests.

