**Methods/design:**

In this study, investigators will recruit 20 community coalitions and 7,200 African-Americans age 50 to 74 to test passive and active approaches to disseminating the Educational Program to Increase Colorectal Cancer Screening (EPICS); to measure the extent to which EPICS is accepted and the fidelity of implementation in various settings and to estimate the potential translatability and public health impact of EPICS. This four-arm cluster randomized trial compares the following implementation strategies: passive arms, (web access to facilitator training materials and toolkits without technical assistance (TA) and (web access, but with technical assistance (TA); active arms, (in-person access to facilitator training materials and toolkits without TA and (in-person access with TA). Primary outcome measures are the reach (the proportion of representative community coalitions and individuals participating) and efficacy (post-intervention changes in CRC screening rates). Secondary outcomes include adoption (percentage of community coalitions implementing the EPICS sessions) and implementation (quality and consistency of the intervention delivery). The extent to which community coalitions continue to implement EPICS post-implementation (maintenance) will also be measured. Cost-effectiveness analysis will be conducted.

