### Toolkit

The EPICS toolkit is a package that includes facilitator training materials (manual, workshop agenda, and certificates); implementation protocol; EPICS curriculum; individual/participant educational materials; and individual/participant incentives. The toolkit was developed and pilot tested during the local and state practice demonstrations. Community coalitions randomized to passive dissemination arms will access all toolkit components except participant incentives via the web. Those randomized to active dissemination will receive all toolkit components via in-person delivery. In the case of individual/participant incentives, delivery will be via US Postal Service for community coalitions in all dissemination arms.

1. Facilitator training: Consistent with principles of Adult Learning Theory, the EPICS facilitator training workshop is skill-based, highly participatory, and provides learners with immediate opportunities to apply new skills and information [14]. A user-friendly Facilitator Training Manual has been developed and tested. The one-and-one-half-day facilitator training workshop introduces basic vocabulary, concepts, and methods of community-based cancer control and instructional strategies for African Americans of varying health literacy. Each community coalition will identify a minimum of five members, in addition to a leader, to complete facilitator training. Community coalitions randomized to passive dissemination arms will download training materials from the National Cancer Institute’s Research Tested Intervention Programs (RTIPs) website (http://rtips.cancer.gov/rtips/index.do) and conduct the training themselves, while those in active dissemination arms will be trained by EPICS developers. The facilitator training workshop consists of three modules that address: principles knowledge (*e.g.*, conceptual framework, intervention overview, and local/statewide demonstration projects); procedural knowledge (*e.g.*, how to implement the three EPICS sessions); and practical knowledge (*e.g.*, how to market the programs and complete the EPICS assessments and measures).

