### Secondary outcome measures

Qualitative and quantitative research methods are useful in gaining insight and understanding of human behavior, and are recommended by Rogers to study the process of an innovation’s adoption. The secondary outcome for the EPICS cRCT is the percentage of clusters and settings implementing the EPICS sessions. In the RE-AIM framework, adoption is concerned with the representativeness of both the setting in which an intervention is conducted and the change agents who deliver the intervention. EPICS implementation is concerned with quality and consistency of the intervention delivery. It refers to the extent to which various components of an intervention are delivered as intended in real-world settings.

The final RE-AIM dimension, maintenance, refers to the extent to which a program or policy becomes institutionalized or part of the routine organizational practices and policies. At the individual level, measuring maintenance requires follow-up contact six-months or more post-intervention. Due to the timing of CRC screening recommendations (*e.g.*, one to ten years), we will not measure individual maintenance, but will focus at the change agent or cluster level, measuring long-term institutional effects. Organizational impact will be measured based on the following calculation, where fidelity is scored 1 to 4 according to the core elements listed in Table 1:

$$\text{Estimate}\;\text{of}\;\text{Impact}=\frac{\%\;\text{clusters}\;\text{adopting}x\%\;\text{implementing}\;\text{x}\%\;\text{institutionalizing}\;\text{EPICS}}{\text{fidelity}\;\text{to}\;\text{core}\;\text{elements}}$$

**Table 1 T1:** EPICS sessions

**#**	**Title**	**Content**
**1**	Introduction to EPICS	This session provides a general overview of colorectal cancer (CRC) facts. Definitions and screening guidelines; fecal occult blood test (FOBT), sigmoidoscopy and colonoscopy; costs; insurance coverage
**2**	Colorectal cancer screening, symptoms and diagnosis	Common symptoms explained. Finding the cause of symptoms through CEA assay, biopsy, x-rays, sigmoidoscopy or colonoscopy. Definition of treatment methods (surgery, chemotherapy, radiation therapy, biological therapy) Clinical Trials; Social support; developing a plan; monitoring success; EPICS colorectal cancer screening goals.

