**3**	Maintaining healthy habits	This session encourages participants to incorporate healthier cooking and eating habits into their lifestyles. It also focuses on CRC screening as an important health habit. Incorporating these healthier lifestyles may potentially confound the effect of the intervention on CRC use.

Adoption is the percent of NBLIC community coalitions approached for participation who did, in fact, participate. Adjustments for attrition will be made using intent-to-treat analysis*.* Implementation is the average percent and extent to which core elements are implemented as intended. Institutionalization is the extent to which NBLIC community coalitions continue to offer EPICS post-implementation.

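### Adoption, a named secondary outcome, has incompatible definitions, and the one restricted to trained coalitions could mask or reverse a difference between arms if some coalitions do not complete training

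*Protocol article*

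**What the plan says.** The protocol article describes adoption in five places.

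- Abstract, Methods/design, among the secondary outcomes: "adoption (percentage of community coalitions implementing the EPICS sessions").
- Secondary outcome measures, opening paragraph: "The secondary outcome for the EPICS cRCT is the percentage of clusters and settings implementing the EPICS sessions".
- Secondary outcome measures, after Table 1: "Adoption is the percent of NBLIC community coalitions approached for participation who did, in fact, participate". The next sentence reads "Adjustments for attrition will be made using intent-to-treat analysis".
- Methods and statistical analysis, Effectiveness: "The proportion of community coalitions and settings aware of EPICS (effectiveness-organizational level) and that deliver it (adoption) will also be determined".
- Methods and statistical analysis, Adoption: "estimating adoption rate (proportion of community coalitions trained that implement EPICS").

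Two other places bear on the trained-only version. Trial timeframe puts randomisation in months one to three and facilitator training in months four to seven. Toolkit says that coalitions in the passive arms download the materials and "conduct the training themselves, while those in active dissemination arms will be trained by EPICS developers".

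**The concern.** The numerator changes (participate, implement, deliver), the denominator changes (approached, trained, no stated restriction) and the unit changes (coalitions, or coalitions and settings). Two analysts who each follow the article could report different adoption rates from identical data.

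The trained-only version has a second problem. Completing training is a status reached after randomisation, and the mode of training is part of what the arms differ in. A coalition that never completes self-run training is a failure of that dissemination strategy, yet it leaves the denominator. A comparison of arms on this rate would no longer be a comparison of the groups as randomised.

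The first key aim is to test passive against active dissemination, so adoption by arm is something readers will look for. The Impact formula also multiplies by the percentage of clusters adopting, so the ambiguity carries into a second reported quantity.

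**Working it through.** The article states no adoption rate and no power for adoption, so there is no figure to reproduce. The check sets the definitions side by side and then applies two denominators to the same assumed counts.

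**Definitions**

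| Place | Numerator | Denominator | Unit |
|---|---|---|---|
| Abstract | implementing | no restriction stated | coalitions |
| Secondary outcome measures, opening | implementing | no restriction stated | clusters and settings |
| Secondary outcome measures, after Table 1 | participating | approached | coalitions |
| Effectiveness | delivering | no restriction stated | coalitions and settings |
| Adoption | implementing | trained | coalitions |

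**Inputs from the article**

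- Coalitions randomised: 20 of 33 (Community coalitions).
- Coalitions per arm: 30 groups × 12 completers = 360 people per coalition, and 1,800 / 360 = 5 (Sample size calculation). Equally, 20 / 4 = 5.
- Pooled, this is 10 passive and 10 active coalitions.

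All counts of trained and implementing coalitions below are assumptions.

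**One arm of five coalitions**

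- 2 trained, both implement: among trained 2/2 = 100%; among randomised 2/5 = 40%.
- 5 trained, all implement: 5/5 = 100% either way.

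On the trained-only rate these two arms look identical.

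**Passive against active, 10 v 10.** In every row all 10 active coalitions train and 8 implement, so the active rate is 80% on both denominators. Differences are active minus passive.

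| Passive trained | Passive implementing | Passive rate among trained | Difference, trained | Passive rate among randomised | Difference, randomised |
|---|---|---|---|---|---|
| 10 | 8 | 80% | 0 points | 80% | 0 points |
| 8 | 6 | 75% | 5 points | 60% | 20 points |
| 6 | 5 | 83% | −3 points | 50% | 30 points |
| 5 | 4 | 80% | 0 points | 40% | 40 points |
| 4 | 4 | 100% | −20 points | 40% | 40 points |

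The first row is the case without distortion. In the others the trained-only rate shrinks, removes or reverses a difference that the randomised denominator shows.

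**All arms together.** Assume that all 33 coalitions were approached, 20 participated and were randomised, 15 trained and 12 implemented. Then:

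- participating / approached = 20/33 = 61%
- implementing / randomised = 12/20 = 60%
- implementing / trained = 12/15 = 80%

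**The approached version by arm.** A coalition that was approached but not randomised belongs to no arm, so this ratio has no clear denominator within an arm.

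**Precision.** For 4/10 v 8/10 the two-sided Fisher p is 0.17. For 2/5 v 5/5 it is also 0.17: the probability of the observed table is C(5,2)·C(5,5)/C(10,7) = 10/120 = 0.083, and the mirror-image table doubles it.

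**The case against.** The strongest reply is that the distortion needs training failures, and the article reports none. Toolkit expects every coalition, in all arms, to put forward at least five members and a leader for training, and Trial timeframe expects training to be finished by month seven. If that happens, trained and randomised coalitions are the same 20. This stands. A reader might infer that the trained-only rate favours the passive arms as a matter of fact; the documents support only that it could.

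No test of adoption between arms is stated either. The Adoption section plans descriptive statistics and comparisons of adopting with non-adopting coalitions, and none of the three hypotheses concerns adoption by arm. This also stands. Comparison by arm is an inference from adoption being a named secondary outcome of a four-arm trial of dissemination strategies.

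A reader might also infer that the approached version is settled before randomisation and so must be equal in every arm. The documents do not establish this. Memoranda of understanding were signed while the project was being developed, but the date of approach is not given, and Trial design mentions consent from coalition members alongside allocation.

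The intent-to-treat sentence could be read as already committing the trial to keep lost coalitions, which would make the Adoption section merely loose wording. That reading is fair, but the two sections then still need to be aligned, because the trained-only denominator says otherwise.

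Finally, the primary outcomes, reach and effectiveness, do not use this definition, and five coalitions per arm support little formal inference. Both points limit the consequence. They do not remove the contradiction, and where rates are mainly descriptive the choice of denominator largely decides the message.

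**Conclusion.** The inconsistency is certain. The current text gives a named secondary outcome at least three incompatible definitions, which differ in numerator, denominator and unit. It does not depend on what a separate analysis plan might add, because the article itself fixes adoption in different ways.

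The risk to a comparison of arms is conditional. It arises only if some coalitions do not complete training and adoption is then reported by arm on the trained-only rate. Under the assumed counts, a 40-point difference among randomised coalitions can show as zero or as 20 points in the opposite direction; with complete training nothing is hidden. The documents give no basis for saying which case will occur.

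This should be corrected. It affects a secondary outcome and the Impact formula, not the primary outcomes.

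**What to change.** Use one definition of adoption throughout. For any report by arm, take coalitions implementing EPICS divided by all coalitions randomised to that arm, and count those lost before or during training as non-adopters. State the settings-level rate separately, with its own denominator.

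Report approached-to-participating as recruitment or uptake, and trained-to-implementing as a descriptive process measure.

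State which of these quantities enters the Impact formula. The new definition should not replace its uptake term by default: that would drop the step from approached to participating and overlap with the formula's separate implementing term.

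The cost is essentially wording, since the article already plans to record participation, implementation and completion of facilitator training. The downside is that reported adoption may be lower, possibly by a lot if many coalitions do not complete training. With five coalitions per arm the rates remain mainly descriptive.

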### Implementation

To evaluate EPICS implementation, the following methods will be employed: train and certify facilitators to deliver educational sessions; implement marketing strategies to enhance visibility; provide on-going technical assistance (TA) to organizations and settings; determine adherence to implementation protocol by passive and active dissemination sites; estimate total number of completers; conduct one-and-one-half day training guided by three modules: principles, procedural and practical knowledge; distribute a monthly newsletter, provide promotional flyers and posters to community coalitions and settings; conduct one-hour monthly teleconferences; assess the nature and quality of TA; measure level of fidelity to delivering sessions as developed; and determine total number of individuals completing the three educational intervention sessions. Descriptive statistics will determine differences in facilitator characteristics, knowledge, attitudes, and beliefs and level of satisfaction with training, the most effective marketing strategies, reasons for not implementing components, duration, and investment and differences facilitator demographic characteristics: education, gender, profession, insurance status, etc. Logistic regression analysis will evaluate variations in the effects of implementation barriers among community coalitions, settings and individual participants.

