**Figure 1 F1:**
[figure not shown]
CONSORT flow diagram for EPICS cRCT.

Randomization at the organizational (community coalition) level has been chosen because this will minimize contamination that may occur if individual participants are randomized. In utilizing cluster randomization, we will focus on community coalitions as the cluster for all study arms, with individuals within their target settings as the secondary unit. We will ensure balance in all four study arms by ordering them into groups based on the total number participating. A computer program generating random numbers between 1 and *n* will be used to assign community coalitions to one of four conditions: web access (WA) to facilitator training materials and toolkits without technical assistance (TA); the same as 1, but with technical assistance (TA); in-person access (IP) to facilitator training materials and toolkits without TA; and in-person access to facilitator training materials and toolkits with TA. Our multilevel approach (*e.g.*, cluster, setting, and individual) promotes widespread dissemination [13]. Community coalitions will be allocated to one of the four arms and informed consent will be obtained from community coalition members and from individual participants.

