2. Implementation Protocol: We also developed and tested a protocol similar to that used in the original CCSIT study and converted it into non-academic language. This 12-step protocol includes procedures to: recruit community partners; schedule sessions; market the program; recruit participants; prepare for the sessions; sort the toolkit; assign facilitators; deliver the sessions; identify ‘completers’ (participants attending all three intervention sessions); monitor screening; submit reports; and get technical assistance.

3. EPICS Curriculum: Individual participants in all study arms will complete three small group educational sessions. These sessions, each approximately one-hour in length, will be conducted the same day/time of the week for three consecutive weeks. This schedule will be formulated by NBLIC community coalitions in conversation with intervention settings at a time likely to solicit the greatest participation.

4. Individual/participant CRC educational materials include three session-specific brochures, CDC consumer education materials, including: Get Smart in Your Family Dinner; Get Smart as You Shop; and CRC Facts on Screening.

5. Individual/participant incentives such as a cookbook, water bottles, shopping bag, and similar items are distributed to individuals completing all three EPICS sessions.

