**Figure 2 F2:**
[figure not shown]
Study overview.

Based on Rogers’ theory, innovations that are simple, such as EPICS, are often adopted more rapidly and lead to a higher degree of sustainability. Diffusion of Innovations Theory addresses the process of adoption and uptake of interventions by a targeted audience. Three key components of this theory make it well-suited to facilitate adoption of EPICS at the cluster and setting levels. Research suggests that the most effective communication strategy is face-to-face exchange [15]. We hypothesized that social support theory, which uses informal communication channels, helped explain the success of EPICS.

We will continue to use informal communication channels (as recommended by Rogers) to reach change agents and early adopters. Change agents are organizations connected to early adopters*,* organizations that will attempt EPICS before other organizations [15]. Rogers’ theory will provide valuable insights into why EPICS is adopted by some NBLIC community coalitions and not by others. In the EPICS cRCT, this theory will:

1. Explain variance in adoption rates: All clusters will complete Barriers and Enablers to Uptake Assessment (which include setting level-specific questions) to measure key attributes.

2. Explore the impact of facilitators on EPICS dissemination: We will compare key attributes and facilitator knowledge, attitudes and confidence (Pre and Post-Facilitator Training Knowledge, Attitudes and Confidence survey).

3. Evaluate fidelity of implementation to determine adherence to EPICS core elements.

4. Examine the relationship between adoption and outcomes: (*e.g.*, cost-effectiveness analysis, CRC screening rates and number of individuals completing all three EPICS sessions).

5. Establish the role of TA*:* Comparing passive and active arms (providing reinforcement and positive feedback in Rogers’ confirmation stage).

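### The role of technical assistance (TA) is assigned to a passive v active comparison, which estimates web v in-person delivery and carries no information on the TA main effect

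*Protocol article*

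**What the plan says.** The Abstract (Methods/design) and the Trial design section define four randomised conditions. The passive pair is web access (WA) without and with TA. The active pair is in-person access (IP) without and with TA; the third condition, for example, is "in-person access (IP) to facilitator training materials and toolkits without TA". TA is therefore one of two crossed factors.

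Three other places bear on TA:

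- **Theoretical framework, item 5.** The aim is "Establish the role of TA", and the means given is "Comparing passive and active arms (providing reinforcement and positive feedback".
- **Toolkit, item 2 (Implementation Protocol).** The 12-step protocol ends with "submit reports; and get technical assistance". The same section makes this protocol part of the toolkit that both passive and active coalitions receive.
- **Implementation (under Methods and statistical analysis).** The listed activities include "provide on-going technical assistance (TA) to organizations and settings", with no arm named.

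Two places keep the four arms apart. The Power analysis section compares each of the other arms, including Web + TA, with web-only. The Cost-effectiveness analysis section compares costs and outcomes of all four strategies.

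**The concern.** A comparison meant to show what TA does must set arms with TA against arms without it. Passive v active does not: TA is present in half of each side. Followed as written, item 5 would report the effect of in-person delivery under the label of TA. A disseminating agency could then pay for TA on the strength of an in-person effect, or drop TA because in-person delivery made no difference. TA personnel time and expenses are among the costs to be collected, so the answer has a practical use.

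The second strand is consistency. Two arms are randomised to no TA, while the toolkit step and the Implementation list mention TA without repeating that limit. Any TA that reached no-TA coalitions would shrink the true TA contrast.

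**Working it through.** **Inputs.** Arms in the order WA, WA+TA, IP, IP+TA, with mean outcomes m1 to m4 (Abstract; Trial design). Assumed enrolment gains over web-only of 25%, 33% and 50% for Web+TA, IP and IP+TA; example web-only rates of 5%, 10% and 20%; 1,800 per arm; two-sided 5% chi-square test (Power analysis). Item 5 names no outcome. Enrolment is used here because it is the outcome with assumptions for each arm.

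**1. The plan's own figure, and how to read the gains.** The article states more than 99% power for each arm v web-only. Without clustering:
- read as percentage points added to the web-only rate, all nine combinations exceed 99%, so the figure reproduces;
- read as relative increases, Web+TA v web-only gives 37.0%, 66.1% and 94.9% at web-only rates of 5%, 10% and 20%, so it does not.

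The article does not say which reading is meant, so both are carried forward. The power figure is not otherwise evidence on this point.

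**2. The two contrasts.**
- Active minus passive: (m3 + m4)/2 - (m1 + m2)/2, weights (-1/2, -1/2, +1/2, +1/2).
- TA minus no TA: (m2 + m4)/2 - (m1 + m3)/2, weights (-1/2, +1/2, -1/2, +1/2).
- Inner product: 1/4 - 1/4 - 1/4 + 1/4 = 0. The contrasts are orthogonal.

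**3. Additive illustration.** Take a delivery effect of 10 points (assumed) and vary the TA effect:

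| True TA effect | Active - passive | TA - no TA |
|---|---|---|
| 0 | 10 | 0 |
| 10 | 10 | 10 |
| 25 | 10 | 25 |

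The passive v active result does not move with the TA effect.

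**4. On the article's enrolment assumptions.**
- Relative reading (1.00, 1.25, 1.33, 1.50): active/passive = [(1.33 + 1.50)/2] / [(1.00 + 1.25)/2] = 1.415/1.125 = 1.26. TA/no TA = [(1.25 + 1.50)/2] / [(1.00 + 1.33)/2] = 1.375/1.165 = 1.18.
- Percentage-point reading (gains 0, 25, 33, 50): active - passive = 41.5 - 12.5 = 29 points. TA - no TA = 37.5 - 16.5 = 21 points.

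**5. How far the zero depends on equal arms.** For an outcome averaged over enrolled people, unequal enrolment would unbalance TA slightly. On the relative reading, the TA share is 1.25/2.25 = 55.6% of passive and 1.50/2.83 = 53.0% of active participants. That gap of 2.6 points is too small to make the contrast informative about TA.

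**6. Estimability and leakage.** With intercept, delivery mode and TA as randomised, the four-arm design matrix has rank 3 of 3, so TA is estimable. It would fall to rank 2 only if every coalition received TA. If a share f of no-TA coalitions received full TA, the Web+TA v Web difference would shrink to (1 - f) of its value: 25 points becomes 18.75, 12.5, 6.25 and 0 at f = 0.25, 0.5, 0.75 and 1. The article gives no value for f. With 20/4 = 5 coalitions per arm there are 10 no-TA coalitions, so one that received full TA would remove about a tenth of the contrast if coalition effects are equal.

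**The case against.** **Item 5 belongs to a theory section.** It is one line on what Rogers' theory will contribute and specifies no estimator. It might mean looking at TA within the passive pair and within the active pair, and a condensed article may leave the detailed contrast to a fuller document. This has some force on severity. But the line does name a comparison, and as worded that comparison is between the pairs. If the within-pair reading was intended, the proposed wording simply says so.

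**The four arms are kept separate elsewhere.** This stands. The Power analysis section has Web + TA v web-only, a TA contrast within web delivery, and the Cost-effectiveness section compares all four strategies. Neither fully replaces item 5: the first is a power assumption and omits IP+TA v IP, and the second leads to incremental cost ratios between neighbouring strategies. The model printed under Primary outcome measures has no explicit TA term.

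**No hypothesis concerns TA.** Also true. H1 and the passive v active comparison of screening rates are intended as such and are unaffected.

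**A reader might infer that TA goes to every coalition and so cannot be estimated.** The article does not support this. The Implementation list never says all. It pools activities across arms: it also lists facilitator training without naming arms, although the Toolkit section has passive coalitions train themselves and the developers train the active ones. The allocation text is explicit about who is without TA. Nor does any section call the monthly teleconferences TA, so they cannot be counted as TA reaching the no-TA arms.

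**Conclusion.** The point holds in two parts of unequal weight.

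The main part is a stated mismatch between aim and comparison in item 5 of the Theoretical framework list. With four equal arms, passive v active is orthogonal to the TA main effect. On the enrolment assumptions it would return 1.26 rather than 1.18, or 29 rather than 21 points. These sizes depend on which reading of the 25%, 33% and 50% gains is taken, and apply only if item 5 is followed literally. The orthogonality itself depends on neither reading.

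The lesser part is that the Toolkit and Implementation sections mention TA without the arm limit set in the Abstract and Trial design. These passages need to be reconciled. Actual leakage is unknown, and the article does not show that any is planned. If TA is delivered as randomised, its effect can be estimated.

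**What to change.** 1. In Theoretical framework, item 5, replace the passive v active comparison with (WA+TA and IP+TA) v (WA and IP), adjusted for web v in-person delivery.
2. In Toolkit item 2 and in the Implementation section, state which arms receive TA, so that both agree with the without-TA arms in the Abstract and Trial design. For the toolkit step, say how it applies to coalitions in those arms.
3. Keep a simple log of any implementation support given to no-TA coalitions, so that departures from allocation can be described.

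The cost is wording in three places and one short log. The allocation, sample size, H1 and passive v active analyses stay as they are.
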